#### Secondary outcome measures

Numeric rating scale

The two single-item 1–10 numeric rating scales (NRS) measure perceived severity of the problem by the parents and estimate the child’s experience [37].

Strength and Difficulties Questionnaire (SDQ).

The validated SDQ has two versions, one for parents (7–19 years) and one for children (11 years and over), which were developed using the ‘diagnostic and static manual of mental disorders classification’ for psychosocial problems, as these problems (anxiety, depression, behavioural disorders and attention deficit hyperactivity disorders) are relatively common among young people. The total score ranges from 0 to 40 points, with established cut-off points at 0–10 (normal), 11–13 (borderline, presence of less serious issues) and above 14 (high) [38-40].

Global perceived effect

The global perceived effect (GPE) instrument is a subjective score that simply shows the perceived change in symptoms during and after treatment, ranging from 1 (much worse) to 9 (complaints have disappeared). The GPE will be administered at MT-WB 2 and MT-WB 3 before the final visit to the physiotherapist.

Pelvic floor muscle function

The following measurements will be done by the physiotherapist at the second (MT-PPT 1) and final visit (MT-PPT 2).

• Digital testing

• Digital testing will be used to measure the ability and reflex action of the pelvic floor muscles (PFM) at rest and during contraction, cough and straining to defecate. The tone of the internal and external anal sphincters and puborectalis muscle will be palpated, and the sensitivity, anal reflex and presence of stool evaluated. Strength, endurance, coordination and the ability to close the rectum will be evaluated by asking the child to contract and relax the PFM, and then to hold the contraction for 30 seconds. At the same time, the pelvic physiotherapist will assess whether the child is contracting the extra-pelvic muscles, like the abdominal, gluteal and adductor muscles.

• Myofeedback

• Myofeedback uses the electromyographic (EMG) signal of the pelvic floor muscles. The level of the EMG signal should increase while contracting, whereas the signal should decrease at relaxation [15,17,41,42]. Given the absence of an assessment instrument to define proper muscle tone of children's pelvic floor, parameters for the male adults will be used [28,29,36,43].

• For the purpose of this study, the small intra-anal PelviRing Anal Probe will be used.

• The baseline tone of the puborectalis, the maximum strength, and maximum strength after 30 seconds, the tone during straining, the fast and slow twitch and the ability to relax will be measured.

• Values are considered abnormal when: (1) The resting tone is higher than 5 μV (hypertonic) or lower than 2 μV (hypotonic), (2) the sub maximal strength after 30 seconds is not equal to the resting tone, (3) the tone during straining is over 5 μV, (4) onset over 0.2 seconds, (5) offset over 0.2 seconds, (6) the resting tone after testing is higher than 5 μV and (7) the tone fluctuates.

• Rectal Balloon Catheter

• Rectal balloon training (RBT) will be used to develop awareness of the sensory threshold and to strain in a proper way. A neoprene rectal balloon attached to a syringe will be introduced into the rectum and slowly inflated with air to imitate rectal contents. Next, the child will be requested to excrete the balloon, as it would do during defecation. Attention will be paid to the effect of the pelvic floor muscles on sensory threshold, urge sensation, maximum tolerated volume and straining. Satisfactory (reflex) reaction of the external anal sphincter or overreactions of the pelvic floor muscles and of the extra-pelvic muscles like those of the trunk, legs, arms or head are recorded at first sensation, urge and maximum urge. The method of straining is left to the child. The ability to strain sufficiently to defecate is recorded. Absence of reaction of the external anal sphincter, immediately before or at sensory threshold, urge and maximum tolerated volume, will be considered abnormal, as are overreactions of the pelvic floor muscles or the extra-pelvic muscles at straining**.**

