## Methods/design

### Trial design, hypothesis and research

To date, there has been little scientific evidence evaluating the effectiveness of pelvic physiotherapy (PPT) in childhood constipation [7,14,29,30]. Therefore we designed a two-armed multicentre randomised controlled clinical trial (RCT). We hypothesise that the combination of standard medical care (SMC) and PPT will prove more effective than SMC alone for the treatment of FC in children aged 5 to 17 years.

Secondary research questions are: (1) Does PPT add to the child’s quality of life, as defined by the strengths and difficulties questionnaire (SDQ), the numeric rating scale (NRS) in relation to the perceived severity of the problem and the global perceived effect (GPE), (2) what values of the pelvic floor muscle function (PFMF) in children can be defined based on the results of the study in clinically relevant subgroups, according to the international continence society (ICS) criteria.

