### Data analysis

After checking for missing data and testing for normality, group differences will be analysed using the Pearson Chi-square test, or likelihood ratio in the case of dichotomous outcomes. Continuous outcomes will be analysed using the independent samples t-test or the Mann–Whitney U test. Adjusted group differences will be analysed using multivariable logistic regression with ordinal variables transformed into dummies, taking into account possible differences in mean number of sessions. Finally, subgroup analyses will be done to establish normal values and observed differences in effectiveness for relevant clinical subgroups.

Data analysis will be done according to the intention-to-treat principle. Characteristics of the study population at baseline will be described. Potential effect modifiers like age and gender [10,14], as well as potential confounders like urinary incontinence, enuresis and abdominal pain will be taken into account [17,47-51]. To assess selection bias, responders and nonresponders will be compared in terms of relevant clinical and demographic variables. Data analysis will be carried out using SPSS version 19.0 (SPSS Inc., Chicago, Illinois). A two-tailed p-value of 0.05 will be considered statistically significant.

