## Discussion

Why publish a study protocol? This study aims to show that pelvic physiotherapy in combination with standard medical care is more effective than standard medical care alone in constipated children. To our knowledge, this article is the first to describe the design of an RCT among children with FC to assess the effect of PPT as an add-on to SMC. The Dutch Pelvic Physiotherapy Protocol (DPPP) presented here is based on the available literature, a survey and a Delphi procedure among experts. Exchanging knowledge and expertise with other researchers is important in order to prevent duplicate research. Consequently, it has been decided to publish the study protocol prior to achieving results.

The DPPP was developed between 2007 and 2009. Given that no studies have so far been published on the effect of PPT in childhood constipation [52] and that a repeat survey on standard PPT among 49 Dutch physiotherapists in 2011 did not yield substantial differences compared to the 2007 survey, we feel this protocol is as up-to-date as possible.

In the absence of an evaluation tool, we will use parameters for male adults to define the proper childhood pelvic floor muscle functions. These values are expected to be similar to the children’s, as is also the opinion of the experts and the literature [36].

Confounding in our trial may arise due to the Hawthorne-effect as a result of differences in number of the protocolised contacts. Although it is expected, based on experience, that the mean number of treatment sessions will be equal, adjusted group differences will be analysed.

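### One set of adult-male EMG limits classifies boys and girls aged 5–17, so age or sex differences in the hypertonic/hypotonic labels are confounded with the unverified fit of the limits, and a sample of constipated children cannot supply normal values

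*Protocol article*

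**What the plan says.** Under Secondary outcome measures (Myofeedback), the protocol article explains its choice of EMG limits: "Given the absence of an assessment instrument to define proper muscle tone" in children, "parameters for the male adults will be used". The same subsection then lists the criteria under the lead-in "Values are considered abnormal when". The first is "The resting tone is higher than 5 μV (hypertonic) or lower than 2 μV (hypotonic"; others set limits for tone during straining (over 5 μV) and for onset and offset (over 0.2 seconds). None is split by age or sex. The Inclusion criteria admit ages 5 to 17 and do not restrict sex.

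The Discussion repeats the choice: "we will use parameters for male adults to define the proper childhood pelvic floor muscle functions". It defends it by saying "These values are expected to be similar to the" children's, citing expert opinion and a reference.

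The article also treats paediatric values as something to be found. The second secondary question asks "what values of the pelvic floor muscle function (PFMF) in children can be defined based on the results of the study", in clinically relevant subgroups. Data analysis plans subgroup analyses to establish normal values. The end of the Discussion says the trial will determine such values in children and that its outcomes will feed a physiotherapy guideline. Data analysis also lists "Potential effect modifiers like age and gender".

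**The concern.** Two statements pull against each other. The Discussion uses adult-male parameters to define proper function in a child; the aims say that the values in children are still to be established. While the first rests on expectation, a label of hypertonic or hypotonic mixes two things: the child's muscle function, and the distance between that child's reference group and adult men. If ordinary tone differs between girls and boys, or between a 5-year-old and a 17-year-old, the labels will differ as well, without any difference in dysfunction.

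The second difficulty is the source of the promised normal values. Every child enrolled has functional constipation, and the article's own background holds that pelvic floor dysfunction causes the complaint in most of these children. Readings from them describe patients. Labelled as normal values and carried into a guideline, they could set a diseased distribution as the reference.

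**Working it through.** The article gives no EMG mean, SD or expected abnormality rate, so there is no figure of the plan to reproduce on this point. Its one computed figure, the enrolment target of 367, rests on the Rome III outcome and does not use EMG.

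**1. Do the limits vary by age or sex?** No. I read the criteria listed under Myofeedback as the adult-male parameters announced just before them. They apply to every child.

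**2. How far could misfit move the labels?** Inputs from the article: limits of 2 and 5 μV for resting tone. Inputs that I assume: a normal distribution, group means m of 3 to 4.5 μV, and SDs of 0.75, 1.0 and 1.5 μV.

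- Share labelled hypotonic = Φ((2 − m)/SD)
- Share labelled hypertonic = 1 − Φ((5 − m)/SD)

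For m = 3 and SD = 1.5: Φ(−0.67) = 0.252 and 1 − Φ(1.33) = 0.091. For m = 4 and SD = 1.5: Φ(−1.33) = 0.091 and 1 − Φ(0.67) = 0.252.

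| SD (μV) | Mean (μV) | Below 2 | Above 5 | Outside 2–5 |
|---|---|---|---|---|
| 0.75 | 3.0 | 9.1% | 0.4% | 9.5% |
| 0.75 | 4.0 | 0.4% | 9.1% | 9.5% |
| 1.0 | 3.0 | 15.9% | 2.3% | 18.1% |
| 1.0 | 4.0 | 2.3% | 15.9% | 18.1% |
| 1.5 | 3.0 | 25.2% | 9.1% | 34.4% |
| 1.5 | 4.0 | 9.1% | 25.2% | 34.4% |

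(Totals are from unrounded shares.) A harmless 1 μV difference between two groups reverses the hypotonic/hypertonic split but leaves the total alone, because 3 and 4 lie equally far from the midpoint of 3.5. A shift that is not symmetric also moves the total: from mean 3.5 to 4.5 it goes from 4.6% to 25.3% (SD 0.75), 13.4% to 31.5% (SD 1.0) or 31.7% to 41.7% (SD 1.5). The straining criterion has only an upper limit, so nothing offsets a shift there.

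**3. Does the misfit favour one arm?** No. The same limits apply in both randomised groups, and allocation is independent of age and sex. Misfit may blunt the flags but does not create a difference between arms. The primary outcome is the absence of functional constipation by Rome III and uses no EMG limit.

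**4. Can the sample yield normal values?** Functional constipation is an inclusion criterion and no unaffected group is measured. The first EMG assessment (M-PPT 1) comes shortly before randomisation, so it covers both arms untouched by trial treatment, but it covers only patients.

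**The case against.** The choice is disclosed and sourced. The article says why adult limits were borrowed, cites literature and expert opinion, and does not present them as paediatric norms. The cited sources cannot be consulted here, so it is open whether they cover girls or young children. That stands: this is an acknowledged assumption with thin visible support, not a concealed error.

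A reader might infer that abnormality rates by age or sex will be uninterpretable. The article does not support so strong a reading. It plans no such rates, names age and gender only as potential effect modifiers, and does not say that its clinical subgroups will be formed from the flags. The raw EMG quantities are to be measured, and Data analysis provides a t-test or Mann–Whitney test for continuous outcomes.

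A reader might also infer that the arms will be compared on dichotomised EMG, with a loss of information. No such comparison is stated, so no loss can be charged to the plan.

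It can also be said that describing measured values needs no adult limits, and that provisional limits may be used while better ones are sought. That is fair, and it is why the remedy is mostly a matter of labelling. It does not reach the point about normal values. Children free of constipation at six months would not fill the gap either: the article does not name them as a reference group, they are selected by response to treatment, and success permits a macrogol maintenance dose below 10 g a day.

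**Conclusion.** The point holds as a limited one about the second secondary question. Adult-male limits are fixed for all children on an expectation of similarity for which the article shows no data. Differences by age or sex in the hypertonic or hypotonic labels are therefore confounded with the fit of the limits, and a sample consisting only of constipated children cannot provide normal values.

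The size is unknown, because no paediatric EMG distribution is given. Under the assumptions above, a 1 μV difference between groups centred at 3 and 4 μV changes the share called hypertonic from 9% to 25% at SD 1.5, from 2% to 16% at SD 1.0, and from under 1% to 9% at SD 0.75, with the share called hypotonic moving the other way. These figures illustrate sensitivity; they do not estimate what the trial will find. The between-arm comparison, the primary outcome and the sample size are not biased. The reason to act is the intended guideline use, and that the remedy needs only data already being collected.

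**What to change.** Three changes, in the Myofeedback text, in Data analysis and in the closing part of the Discussion:

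1. Answer the second secondary question with the raw EMG readings at M-PPT 1: median and 5th to 95th centiles by sex and age band, set beside the adult-male limits. This turns the expectation of similarity into something a reader can inspect.
2. Report the listed flags only as lying outside the adult-male range, as a provisional description.
3. Replace the term normal values with values in children with functional constipation, including where guideline use is mentioned.

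The changes concern how results are reported, not how any child is assessed or treated. The cost is one extra table and some wording; no visit, measurement or participant is added. The downside is that the normal/abnormal label and the claim to normal values are no longer headline results. Age bands should be few: with three bands and an assumed even split, 367 / (2 × 3) is about 61 children per cell, and 5% of 61 is about 3 children beyond each outer centile, so the centiles should carry confidence intervals.

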### Power of the study

The sample size of this study has been calculated on the basis of a clinical difference of minimal relevance in terms of proportions. The success rate (absence of FC) of the controls has been set at 60% [30,44-46]. There is no published PPT success rate but it is estimated to be 75%. Based on a two-sided effect, an alpha of 0.05, a power of 80% and an expected drop-out rate of 20%, at least 367 children should be enrolled in this study.

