### Randomisation and blinding

Randomisation will be based on a list of random numbers generated by a computer in a 1:1 ratio. Concealed randomisation will take place immediately after the second visit to the physiotherapist. Blinding of practitioners, children and outcome assessor is impossible. However, the investigator and parents are blinded for the web-based and PPT baseline measurements and the diary data.

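### The enrolment target of 367 falls slightly short of the stated 80% power at the stated 20% drop-out: power is about 79%, and the matching target is about 380

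*Protocol article*

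**What the plan says.** All the inputs are in the protocol article, under Power of the study and Randomisation and blinding:

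- Control success: "The success rate (absence of FC) of the controls has been set at 60"%.
- Experimental success: "There is no published PPT success rate but it is estimated to be 75"%.
- Sidedness: "Based on a two-sided effect".
- Error rate, power, attrition and result: "an alpha of 0.05, a power of 80% and an expected drop-out rate of 20%, at least 367 children should be enrolled".
- Allocation: "Randomisation will be based on a list of random numbers generated by a computer in a 1:1 ratio".

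The Data analysis section names the Pearson chi-square test, or the likelihood ratio, for dichotomous outcomes. The article does not give the evaluable number, the sample size formula, or the way in which drop-out was applied.

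**The concern.** If 20% of those enrolled are lost, 80% remain. The enrolled number must therefore be the evaluable number divided by 0.8, which is the same as multiplying by 1.25. Multiplying by 1.2 is a common slip and leaves only 1.2 × 0.8 = 96% of the evaluable children required. The printed target is what that slip would give under one standard formula. If so, power, drop-out and enrolment cannot all hold as printed: either the power or the tolerated drop-out is a little overstated. The target governs a three-year recruitment period, and readers will take the power statement at face value.

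**Working it through.** **Inputs.** p1 = 0.60 and p2 = 0.75, so the difference is 0.15 and the mean is 0.675. Two-sided alpha 0.05 (z = 1.960), power 80% (z = 0.842), 1:1 allocation, drop-out 20%, 367 enrolled. (1.960 + 0.842)² = 7.849 and 0.15² = 0.0225.

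Variance terms:
- pooled: V0 = 2 × 0.675 × 0.325 = 0.43875
- unpooled: V1 = 0.60 × 0.40 + 0.75 × 0.25 = 0.4275

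**Step 1. Reproduce 367.** With the pooled variance in both terms:

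n per arm = 0.43875 × 7.849 / 0.0225 = 153.05, or 306.1 in total.

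306.1 × 1.2 = 367.3, which matches the printed figure to rounding. 306.1 / 0.8 = 382.6, which does not.

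**Step 2. Evaluable and enrolled numbers under the standard two-sided formulas without continuity correction.**

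| Formula | n per arm | Evaluable total | × 1.2 | / 0.8 |
|---|---|---|---|---|
| Pooled in both terms | 153.05 | 306.1 | 367.3 | 382.6 |
| Pooled under the null, unpooled under the alternative (matches Pearson chi-square) | 151.9, so 152 | 304 | 364.8 | 380 |
| Arcsine | 151.2, so 152 | 304 | 364.8 | 380 |
| Unpooled | 149.1 | 298.3 | 357.9 | 372.8 |

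The second row is (1.960 × √0.43875 + 0.842 × √0.4275)² / 0.0225. Rounded up to whole children per arm, the unpooled row is 150 per arm, 300 evaluable and 375 enrolled. No row divided by 0.8 gives 367. A continuity correction raises the evaluable number to 326–330 and the enrolled number, after division by 0.8, to 408–413, which is further away.

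**Step 3. What 367 delivers at 20% drop-out.** 367 × 0.8 = 293.6 evaluable, or 146.8 per arm.

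- Pooled in both terms: Φ(0.15 × √(146.8 / 0.43875) − 1.960) = Φ(2.744 − 1.960) = 78.3%.
- Formula matching the planned test: Φ((0.15 × √146.8 − 1.960 × √0.43875) / √0.4275) = Φ((1.817 − 1.298) / 0.654) = 78.6%.
- Unpooled: Φ(0.15 × √(146.8 / 0.4275) − 1.960) = Φ(2.780 − 1.960) = 79.4%.
- Exact enumeration of the uncorrected Pearson chi-square test: 79.1% at 147 + 147, and 78.8% at 147 controls + 146 physiotherapy.

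For comparison, exact power is 79.9% at 151 per arm and 80.3% at 152 per arm. This supports 304 evaluable as the requirement for the planned test.

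**Step 4. Drop-out that 367 tolerates at 80% power.** 1 − 306/367 = 16.6%; 1 − 304/367 = 17.2%; 1 − 298.3/367 = 18.7%. For the planned test this is about 17%.

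**The case against.** **The mechanism is not documented.** A reader might infer that the protocol demonstrably multiplied by 1.2. The article shows no formula, evaluable number or inflation step. The exact match needs the pooled variance in both terms; the formula that fits the planned test gives 304 × 1.2 = 365. This objection stands: the ×1.2 step is a strong inference, not a stated fact. The shortfall in step 3 does not depend on it.

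**There is no single correct target of 383.** A reader might take 306 / 0.8 = 383 as the right number. It is right only for the formula inferred in step 1, which is slightly conservative: exact power at 153 per arm is already 80.6%. The planned Pearson test gives 380, and the unpooled formula with correct division gives 373–375, within about 2% of 367. This also stands.

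**The loss is small against other uncertainty.** The 75% is an estimate without a published source. At 147 per arm, exact power is 73.1% if the physiotherapy rate is 74% and 84.4% if it is 76%, so one percentage point in that assumption moves power by 5 to 6 points. This limits the importance of the point but does not make the printed combination correct.

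**The target is a minimum.** Recruiting 380 would comply with the text as written. But a minimum is presented as sufficient for the stated power, and this one lies below what every formula above requires.

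**Conclusion.** The point holds as a small arithmetic inconsistency. Under the protocol's own assumptions (60% against 75%, two-sided 0.05, 1:1, 20% of enrolled children without an evaluable outcome), 367 enrolled gives about 79% power, not 80%. The shortfall is 0.6 to 1.7 points by formula and about 1 point by exact calculation of the planned test. In children, 367 is 13 short of the 380 that matches the planned test (13/380 = 3.4%), and about 6 to 16 short across the formulas.

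The conclusion does not depend on which of these formulas was used, since none reaches 80% at 294 evaluable children. It does rest on reading drop-out as the share of enrolled children whose outcome is lost, spread evenly over the arms.

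It would go too far to say that the trial is materially underpowered because of this step. No test, error rate or analysis is affected, and a loss of about one point does not support that reading.

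**What to change.** Keep 367 and restate what it provides: about 79% power at 20% drop-out or, equivalently, 80% power at about 17% drop-out. In the same sentence, give the formula, the evaluable number and the inflation step, for example 304 evaluable for the Pearson chi-square test and 304 / 0.8 = 380 enrolled for a full 80%. This is a change of wording only; the cost is a slightly less favourable stated figure.

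If the sponsor prefers to keep both 80% power and 20% drop-out, the target becomes about 380, which costs 13 more children.
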